#### Sample Recruitment

Contact with the participants will be established through consultations with the nurse case manager of the basic primary care team of each participating center or the consultations with the hospitals belonging to the scope of the study and patient associations. Once they have ensured that the patient meets the eligibility criteria, the patient will be invited to join the study.

### Evaluation of Effectiveness

#### Sample Characterization, Primary and Secondary Assessment Variables, and Data Source.

See summary in Tables 2 and 3.

**Table 2 table2:** Measurement, recording, and data source of variables of characterization.

Type of variable		Register rank/format	Measurement	Source of data
**Characterization: sociodemographic**				
	Sex	Male Female	Registration	Medical history
	Age	18-99	Registration	Medical history
	Marital status	Single Married Widower Divorced/separated	Registration	Registration
	Nationality	Spanish European Union Rest of Europe North America Latin America Africa Asia Other	Registration	Registration
	Education level	No education Primary school Secondary school University degree Master’s degree Doctorate	Registration	Registration
	Occupation	Employed Self-employed Unemployed Retired Permanently disabled Homemaker Student Other	Registration	Registration
**Characterization: clinical**				
	Main diagnosis	ICD-9-CM^a^ codes: 402.01 402.11 402.91 404.01 404.11 409.91 428.x	Registration	Medical history
	Years since diagnosis	0-100	Registration	Medical history
	Other secondary chronic pathologies	ICD-9-CM codes	Registration	Medical history
	HF^b^ signs/symptoms (dyspnea, orthopnea, fatigue, edema, oliguria, paroxysmal nocturnal dyspnea, high venous pressure, crackles R3/R4, murmurs and hepatomegaly)	Yes No	Registration or exploration or anamnesis	Medical history
	Cardiovascular risk factors (smoking, diabetes mellitus II, obesity [weight/BMI], hypertension, previous heart disease, dyslipidemia)	Yes No	Registration or exploration or anamnesis	Medical history
	HF functional classification (establishes the functional severity of HF based on stress tolerance)	I: No limitation. Regular physical activity does not cause dyspnea, fatigue, or palpitations. II: Slight limitation. Usual physical activity causes dyspnea, fatigue, or palpitations. III: Marked limitation (minor activities cause symptoms). IV: Inability to perform any activity. Symptoms even at rest.	NYHA^c^ Functional Classification [31]	Registration medical history

^a^ICD-9-CM: International Classification of Diseases, 9th revision, Clinical Modification.

^b^HF: heart failure.

^c^NYHA: New York Heart Association.

**Table 3 table3:** Measurement, recording, and data source of variables of main and secondary responses.

Type of variable		Register rank/format	Measurement	Source of data
**Of main response**				
	Health literacy	0/50	HLS-EU-Q47^a^ [36]	Registration
		1-5/indicator	NOC^b^ code: 2015 [29]	Nursing record
	Self-management	1-5/indicator	NOC codes: 3102; 1803; 1830 [9,40]	Nursing record
		12-60	European Heart Failure Self-Care Behavior Scale [41]	Nursing record
	Number of readmissions 1m;12m	0-99	Registration	Registration medical history

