#### Sample Size

The HL will be selected as the main outcome to evaluate the effectiveness. This outcome will be measured using the Spanish version of the 47-Item European Health Literacy Questionnaire (HLS-EU-Q47), which achieved a mean score of 32.88, over a possible range of 0 to 50 points, with an SD of 6.10 in the study setting [36]. An increase of at least 10% in the score will be considered clinically relevant due to the mHealth intervention. Accepting an α risk of .05 and a β risk of .90 in a bilateral contrast, 118 participants were needed in every group. A loss to follow-up rate of 30% was considered. However, the calculation is based on a minimum reference of sample observations, so an effort will be made to recruit as many participants as possible to increase the precision of the estimates.

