### Data Analysis: Data Encoding

A data matrix will be created, and data will be processed statistically using SPSS, version 22 (IBM). Statistical significance will be set at 95% (α=.05).

A uni-bivariate descriptive analysis will be performed to determine the sample distribution for each of the variables studied, both for the total sample and for each group. The characterization variables will be summarized using descriptive statistics, expressing qualitative variables in terms of frequency and percentages and quantitative variables in terms of mean and SD.

Before the analysis, the normality of the variables will be evaluated using the Kolmogorov-Smirnov and Shapiro-Wilk tests. Baseline differences in the variables related to the sample profile between the intervention and control groups will be compared using the Student *t* test when these are normally distributed and the nonparametric Mann-Whitney *U* test in case they are not. Differences between dichotomous qualitative variables will be established using the chi-square test or Fisher statistic when appropriate.

A contrast of means will be applied to test the efficacy of the intervention in terms of the normality distribution of the variables. The results will be analyzed using the nonparametric Wilcoxon signed-rank test, which will allow us to check if there are differences between 2 populations from 2 dependent or related samples, or the Student *t* test for normally distributed samples. For independent samples, the nonparametric Mann-Whitney *U* test will be used.

The strength of the relationship between continuous data will be determined from the Pearson or Spearman correlation. The intraclass correlation coefficient will be used if it is necessary to measure concordance between measurements at different times of the study. To identify sociodemographic and clinical characterization variables (independent variables) related to the intervention and the different response variables (dependent variables), multivariate, linear, logistic, or Cox proportional analyses will be performed, as appropriate for each response variable.

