### Strengths

With the aim of overcoming the aforementioned limitations, a qualitative analysis of the risks has been carried out and has been prioritized according to the factor of exposure and urgency.

Randomized controlled trials are considered the “gold standard for assessing efficacy in clinical research and constitute evidence for treatment” [46]. By adopting such a trial and ensuring internal and external validity, we maximized the robustness of our study.

In addition, the multidisciplinary nature of this project is evident in the composition of the research team (psychologist, nurses, physicians, computer engineers), in the incorporation of professionals and patients for its development, and in the association of the 2 public organizations involved in it.

Finally, the cross-cutting nature of this project is reflected in the consideration of the different dimensions of health and the different levels of health care (primary and hospital care). By contrast, the main variable of this project (HL) has a cross-cutting nature as it has been recognized as a basic social determinant for improving health outcomes.

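### The Sample Size section names one main outcome, the HLS-EU-Q47, but Table 3 lists three constructs and eight measures or time points as main response, with no rule for which decides the trial

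*Protocol article*

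**What the plan says.** The Sample Size section is singular about the main outcome: "The HL will be selected as the main outcome to evaluate the effectiveness". It then fixes the instrument: "This outcome will be measured using the Spanish version of the 47-Item European Health Literacy Questionnaire (HLS-EU-Q47"). The mean, SD and relevant difference in that section all belong to this questionnaire. The Strengths section repeats the choice: "the main variable of this project (HL) has a cross-cutting nature".

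Table 3 has a block headed "Of main response" and a separate block for secondary responses. The main block contains:

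- health literacy, by the HLS-EU-Q47 and also by "NOC^b^ code: 2015 [29"];
- self-management, by "NOC codes: 3102; 1803; 1830 [9,40"] and by the European Heart Failure Self-Care Behavior Scale;
- readmissions, entered as "Number of readmissions 1m;12m".

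The NOC outcomes are recorded from 1 to 5 for each indicator. The Data Analysis section sets one level for everything: "Statistical significance will be set at 95% (α=.05"). The article does not say which main response decides the trial, or whether one, some or all of them must succeed.

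**The concern.** The two places give different primary sets. An analyst working from the Sample Size section would base the conclusion on one questionnaire. An analyst working from Table 3 could present any of several measures as a main result at .05, and most of those measures played no part in sizing the trial. Health literacy itself has two instruments in the main block, so naming the construct does not settle the choice either.

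What is at stake is the meaning of a positive result. With one deciding outcome, the two-sided false-positive rate is the nominal 5%. With several candidates and no stated rule, the rate depends on a choice that the protocol leaves open. The Results section adds to the uncertainty, because it predicts significant group differences across primary and secondary variables together.

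**Working it through.** **The plan's own figure.** Inputs from the Sample Size section: mean 32.88, SD 6.10, relevant change 10% (0.10 × 32.88 = 3.288 points), two-sided α .05. The stated β of .90 is read here as power .90. The normal-approximation formula is n = 2(z₀.₉₇₅ + z₀.₉₀)² × SD² / δ² = 2 × (1.960 + 1.282)² × 6.10² / 3.288² = 72.3, so 73 per group. Allowing for 30% loss, 73 / 0.70 gives 105. The stated 118 is not reproduced. That is a separate matter and does not affect this point. What matters here is that every input belongs to the HLS-EU-Q47.

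**Count of main-response entries in Table 3.**

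| Construct | Entries | Number |
|---|---|---|
| Health literacy | HLS-EU-Q47; NOC 2015 | 2 |
| Self-management | NOC 3102, 1803, 1830; self-care scale | 4 |
| Readmissions | 1 month; 12 months | 2 |
| Total | | 8 |

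One of the eight has a sample size basis and seven do not. If each NOC indicator were analysed separately, the number would be larger.

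**Error rate under different success rules, each test at two-sided .05 and no true effect.**

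- Only the HLS-EU-Q47 decides: 5%.
- Any of eight, independent: 1 − 0.95⁸ = 0.337.
- Any of eight, common correlation ρ (assumed; simulated with 400,000 draws of eight equicorrelated z-tests): 0.30 at ρ = 0.3, 0.25 at ρ = 0.5, 0.19 at ρ = 0.7 and 0.12 at ρ = 0.9.
- Any of three, one independent test per construct: 1 − 0.95³ = 0.143.
- All must be significant: below 5%.

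**What an equal alpha split would cost.** Splitting over eight gives .05/8 = .00625. The formula above, with this level and power .90, gives 112 evaluable per group, or 112 / 0.70 = 160 with 30% loss. For the HLS-EU-Q47 at .00625, power is 92.0% if 118 per group are evaluable. It is 76.3% if 118 includes the loss and 82 remain (118 × 0.70 = 82.6, rounded down).

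**The case against.** The strongest defence is that the protocol already answers the question. Its Sample Size section names health literacy, names the instrument and sizes the trial on it. Table 3 is a table of measurement, recording and data sources; it lists instruments, not hypotheses. Nothing in the Data Analysis section says that each NOC code or each readmission window will be tested separately for efficacy. A multiplicity procedure is commonly left to the statistical analysis plan, which is not shown, so its absence from a condensed article is no fault.

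Much of this stands. A reader might infer that the trial has a one-in-three chance of a false claim. The documents do not support that, because the 34% needs both an any-of success rule, which is nowhere stated, and independence. Independence fits poorly: two entries measure health literacy, four measure self-management, and the 1-month readmission count may be contained in the 12-month count. Nor is eight a documented number of tests; it is the number of listed measures and time points.

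What the defence does not remove is the conflict over which outcome is primary. Table 3 separates main from secondary responses, so the placement cannot be dismissed as a mere inventory. An analysis plan could not apply a multiplicity rule without first overriding either the Sample Size section or Table 3.

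It is also fair to say that the objective in the Abstract covers self-management as well as health literacy. Demoting self-management therefore has a real cost, and the sponsor may prefer to keep it confirmatory under a stated rule.

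**Conclusion.** The point holds as an inconsistency in the definition of the primary outcome. One outcome is named and sized in the Sample Size section; three constructs with eight measures or time points are labelled main response in Table 3; seven of the eight have no sample size basis; and one general α covers them all.

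The effect on the error rate is conditional. It is nil (5%) if the HLS-EU-Q47 alone decides. Under an any-of rule, it is about 12-30% for assumed common correlations of 0.9-0.3, 34% for eight independent tests, and 14% for one independent test per construct. The correlations are assumptions, since the documents give none. The protocol does not say which rule applies, and that gap, not any single percentage, is the defect.

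**What to change.** Align Table 3 with the Sample Size section. Keep as sole main response the HLS-EU-Q47 total score, compared between groups at one named post-intervention time point, at two-sided .05. The time point has to be named because Table 1 marks three months for the post-intervention evaluation (stage 6). Move NOC 2015, the self-management measures and both readmission counts to the secondary block.

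If the sponsor wants self-management or readmissions to carry a confirmatory claim, it should pre-specify either its own fixed testing order after the HLS-EU-Q47 or an alpha split. The documents offer no basis for one particular order, so the choice is the sponsor's. A fixed order leaves the HLS-EU-Q47 test at .05. An equal split over eight would call for 112 evaluable per group (160 with 30% loss) to keep 90% power on the HLS-EU-Q47.

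The basic change is to table labels and analysis wording, needs no added participants, and should be made before the group coding is revealed. Its downside is that self-management and readmissions can no longer be stand-alone headline claims.

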**Secondary response**				
	Personal autonomy basic activities of daily living	0-100	Barthel Index [35]	Registration
	Personal autonomy instrumental activities of daily living	0-8	Lawton-Brody Index [42]	Registration
	Therapeutic adherence	0-4	Morisky-Green Adaptation Questionnaire [43] and Recipe XXI	Registration
	Vital forecast	0-30	PROFUND Index [44]	Registration
	Satisfaction with service	0-10	Satisfaction Scale	Nursing record
	Mobile health device satisfaction	1-5	Satisfaction Scale	Built-in mobile health device registration

^a^HLS-EU-Q47: 47-item European Health Literacy Questionnaire.

^b^NOC: Nursing Outcomes Classification.

#### Security Variables

No adverse effects of patients’ exposure in the experimental group were considered, so no safety variables were included in the study.

#### Data Collection and Custody

Participating nurses and physicians will be responsible for data recording during all stages of the intervention (before training) and the collection and custody of informed consent (Multimedia Appendix 1). A password-coded data file will be created for researchers for the collection of a case. The necessary technical and logistical means will be established to ensure that the processing, communication, and transfer of personal data of all participants comply with the provisions of Organic Law 15/1999 of December 13 to protect personal data [45].

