**Methods:**

This is a randomized, multicenter, blinded clinical trial evaluating 2 groups, namely, a control group (standard clinical practice) and an intervention group (standard clinical practice and an ad hoc designed mHealth intervention previously developed), for 12 months.

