#### Description of the Intervention

The mHealth app aimed at empowering HL and self-management of the patients with multimorbidity with HF and complex health needs. It will be developed ad hoc based on the information obtained from the consensus sessions of experts (patients and professionals) and in accordance with the gamification methodology [39]. Although the final choice of the content will depend on the resulting decisions of the experts, it is intended to offer information and resources to the patient according to the level of HL identified and considering the main actions recommended to be incorporated to improve the overall health outcomes of these patients [12]. Thus, the participants in the experimental group will receive the mHealth app and will agree with the health care professional on 3 objectives related to the self-management of their disease, which they will have to achieve within a proposed period, being assisted by the mobile app, which will provide feedback and reinforcement in the achievement of these objectives. The stages and timing are described in Table 1. The intervention carried out in the control group participants will be based on usual clinical practice. Like the experimental group, they will agree with the health professional on 3 objectives they will have to achieve within the proposed time frame. This process (evaluation of the efficacy of the mHealth intervention with 2 groups) will last 12 months.

**Table 1 table1:** Stages of intervention.

Stage	Description	Timing (months)												
0	Detection of potential study participants. Presentation of the project and collection of informed consent.	✓^a^												
1	Baseline data collection for both groups.	✓												
2	For both groups, the patient and the practitioner will agree on the first health goal. On an individual basis, the nurse will present the main aspects related to the use and management of the app to the members of the expert group. The patient’s expectation of self-efficacy in using the app will be assessed to prevent adherence problems concerning the use of mobile health and difficulties in using the app (digital literacy) will be resolved.	✓	✓	✓										

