3	The patient will come for a consultation to check compliance with the chosen objective. If necessary, a simulation test will be performed to confirm that the challenge has been met. At the end of this stage, the patient and the multidisciplinary team will agree on the second objective.			✓	✓	✓	✓							
4	Check compliance with the second objective. Perform simulation test, if required. At the end of this stage, the patient and the multidisciplinary team will agree on the third objective.						✓	✓	✓	✓				
5	Check compliance with the third objective. Perform simulation test, if required.									✓				
6	Postintervention evaluation: all health objectives were achieved by the patient and postintervention evaluation is performed										✓	✓	✓	
7	Follow-up	At 12 months after the intervention												

^a^✓: achievement record.

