#### Masking

Because of the characteristics of the study, it is not possible to blind it to the participants or to the researchers who will carry out the intervention. However, it will be masked to the researchers who will perform the effectiveness evaluation and data analysis. For this purpose, the coding of the randomization variable will be hidden from them and will be guarded by a person outside the project selected by the principal investigator. In this way, it will not be possible to know which groups received the intervention until the analyses are completed.

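### The trial is described as blinded with a masked effectiveness evaluation, but site staff who generally know the arm record the outcome data, including main responses taken from the nursing record

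*Protocol article*

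**What the plan says.** The Methods part of the abstract states: "This is a randomized, multicenter, blinded clinical trial evaluating 2 groups". The Masking section is more candid. It says that "it is not possible to blind it to the participants or to the researchers who will carry out the intervention", but then claims that "it will be masked to the researchers who will perform the effectiveness evaluation and data analysis". The means it gives is that the coding of the randomization variable is hidden from these researchers and kept by someone outside the project until the analyses are complete.

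Data Collection and Custody assigns the recording differently: "Participating nurses and physicians will be responsible for data recording during all stages of the intervention". Table 1, which sets out the stages of the intervention, includes as stage 6: "Postintervention evaluation: all health objectives were achieved by the patient and postintervention evaluation is performed". At stage 2, on an individual basis, "the nurse will present the main aspects related to the use and management of the app", and difficulties with the app are resolved. In both arms the professional or team agrees objectives with the patient, and compliance with them is checked at stages 3 to 5.

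Table 3 lists among the main responses NOC 2015 for health literacy, and NOC 3102, 1803 and 1830 and the European Heart Failure Self-Care Behavior Scale for self-management. All have the nursing record as their source. The HLS-EU-Q47 and readmissions are also main responses, but their sources are given as registration and registration medical history.

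**The concern.** Masking of outcome assessment matters most where an outcome involves judgement. NOC indicators are rated 1 to 5, and a rater who knows that a patient had the app may score more generously without intending to. The article also states in its Results and Discussion that the experimental group is expected to improve and to differ from control, so any such bias has a likely direction. If readers take the blinded label and the masked evaluation at face value, they will treat a difference on these main responses as protected against detection bias when the described procedures do not protect it.

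**Working it through.** **Comparing the statements**

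1. *Who is said to be masked.* The Masking section names two functions, effectiveness evaluation and data analysis.
2. *Who records the outcome data.* Data Collection and Custody gives recording at all stages to participating nurses and physicians. Stage 6 of Table 1 is the postintervention evaluation, so its data fall to them.
3. *Do they know the arm?* Only the experimental group receives the app. A nurse introduces it to each of these patients, the staff resolve problems with it, and later visits check objectives pursued with its help. Site staff will generally know the arm.
4. *Does the stated mechanism mask them?* Concealing the coding of the group variable works for someone who sees a data file with unlabelled groups. It cannot work for someone who has seen the patient receive the app. The article names no separate masked assessor.
5. *Which outcomes are exposed?* Those sourced from the nursing record: the four NOC outcomes and the self-care scale. The article does not say who scores the self-care scale or who administers the HLS-EU-Q47.

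**What a rating shift would do (illustration)**

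The article gives no figure for this bias, so there is none to reproduce.

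Inputs: 118 per group and 30% loss, from Sample Size. If the loss comes off the 118, then 118 × 0.70 = 82.6, taken as 83 analysed per arm. The rating shifts b, in SD units, are assumptions.

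With no true effect and a two-sided 5% test, the standard error of the standardised difference is √(2/n), and

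type I error = P(|Z + b/√(2/n)| > 1.96).

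For n = 83, √(2/83) = 0.155.

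- b = 0.10: 0.10/0.155 = 0.64, giving 0.099, about 10%.
- b = 0.25: 0.25/0.155 = 1.61, giving 0.36, about 36%.

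If instead all 118 per arm are analysed, √(2/118) = 0.130, and b = 0.10 gives about 12%. A larger sample makes a fixed bias more likely to reach significance.

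**The case against.** The strongest reply is that the article discloses the unblinding. The Masking section says plainly that participants and intervention staff cannot be blinded, and Study Design does not use the word blinded. Recording data and evaluating effectiveness could be separate tasks, since Data Collection and Custody speaks separately of researchers and their password-coded file. Table 1 does not name who carries out stage 6, the phrase about training in the recording sentence is unclear, and a condensed article may leave the administration of each instrument to the full protocol.

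Part of this stands: the defect is an overstated property, not a concealed one. But separating the tasks does not rescue the claim. If evaluation means work on coded data, then only the analysis is masked and outcome assessment is not. If it means assessing patients, it conflicts with the recording arrangement. The abstract's label is unqualified on either reading.

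Several stronger inferences are tempting but unsupported:

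- *The nurse who introduced the app scores that patient's outcomes.* The article does not say so.
- *The self-care scale is nurse-rated.* The nursing record is named as a data source, not as the scorer.
- *The outcome behind the sample size, the HLS-EU-Q47, is nurse-rated.* Its source is registration, and its administration is not described.
- *The NOC scores must leave the main responses.* That is a trade-off for the investigators, and the reason weakens if a masked rater is used.
- *Self-completed questionnaires would be blinded.* Patients know their arm.

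**Conclusion.** The concern holds as an inconsistency about blinding status. The abstract and the Masking section claim a property that the described data collection does not deliver for main responses drawn from the nursing record. What the article supports is open-label delivery and assessment with masked data analysis. This rests on the text alone and needs no numerical assumption.

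How much bias would follow cannot be derived from the article. The 10% and 36% error rates depend on assumed shifts of 0.10 and 0.25 SD and on 83 analysed per arm, and Sample Size does not make clear whether 118 is before or after the allowance for loss. They show only that modest shifts would matter at this sample size. They do not estimate the bias in this trial.

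**What to change.** - Make the abstract, Masking, and Data Collection and Custody agree by describing the trial as open-label with masked data analysis.
- State who administers and scores each main response after the intervention, and whether that person knows the arm.
- Interpret main responses from the nursing record as unmasked assessments open to detection bias.
- Claim masked evaluation only for outcomes whose postintervention rating is made by existing staff who neither treat the patient nor know the arm. Both arms are randomized within each centre, so whether such staff are available must be checked; the article does not show it.
- Where feasible, have patients complete the questionnaires without help from the treating nurse. This limits staff influence but does not blind the patient.

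The set of main responses need not change. The cost is rewording and a less favourable blinding label, plus staffing of the postintervention visit for any outcome where masked rating is to be claimed.
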